### Statistical methods

Distribution balance of PCa clinical characteristics such as TNM stage at diagnosis, Gleason score and PSA at time of diagnosis will be presented in a patient characteristics table, stratified by study arms. Categorical variables are displayed as absolute count frequencies and relative frequencies, that is, proportion within study arm. Continuous variables are presented as median and IQR. Minimum and maximum values are not shown to ensure anonymity of the participants.

Recurrence-free survival, that is, time from ADT initiation to castration resistance, will be analysed by using Kaplan-Meier (KM) estimator, stratified by study arm. The statistical significance of the difference between the survival estimates is tested with log-rank test. No adjustments will be used for KM estimator as the study intervention is randomised. Risk of death, as well as risk for occurrence of adverse tumour traits among men receiving atorvastatin compared with men receiving placebo will be estimated using Cox proportional hazards regression.

Univariate analysis of changes in serum lipid levels is performed by calculating the difference after—before for each participant. The statistical significance of the difference between the study arms is analysed by Mann-Whitney U test (or by t-test if under normality). These results are complemented with boxplots. Multivariable analysis for difference in serum lipid levels between the study arms are performed by fitting a logistic regression model such that the study arm is used as the response variable whereas lipid level differences are used as predictors (ie, each lipid level difference as an independent predictor). Lipid levels are expected to display heavy multicollinearity; therefore, variance inflation factors (VIF) are calculated for each coefficient afterwards, and possible adjustments made by dropping predictors with extreme VIFs (>10).

The occurrence of adverse tumour genomic traits will be analysed by calculating the proportion of participants developing adverse tumour genomic traits. The statistical significance between the proportions is tested by proportions test.

The WHOQOL-BREF patient-reported outcome (PRO) of the quality-of-life is analysed by tabulating absolute and relative frequencies. χ^2^ test for homogeneity is used to test the statistical significance of the difference between the study arms of each PRO item.

Subgroup analyses will be performed stratified by type of ADT or antiandrogen therapy initially selected; GnRH agonists/antagonists, antiandrogen, orchiectomy or other. Men who start with antiandrogen therapy often change to GnRH agonists/antagonists or orchiectomy when PSA increases during ADT. This is allowed and PSA recurrence during antiandrogen therapy is not considered as disease progression as serum testosterone needs to be at castrate level as well for meeting the primary endpoint.

Another subgroup analysis will be stratified by whether or not the participants have received local therapy (radiation or surgery) for PCa in addition to ADT and by type of additional therapy participant has received; docetaxel, abiraterone, enzalutamide or apalutamide at hormone-sensitive stage in addition to ADT.

All analyses will include only participants with available data, imputations will not be used. Detailed statistical analysis plan is published before final data analysis. All analyses are performed using SPSS V.27, Stata V.17 and R V.4 statistical softwares.

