**Methods and analysis:**

In this randomised placebo-controlled trial, a total of 400 men with de novo metastatic prostate cancer or recurrent disease after primary treatment and starting ADT will be recruited and randomised 1:1 to use daily 80 mg of atorvastatin or placebo. All researchers, study nurses and patients will be blinded throughout the trial. Patients are followed until disease recurrence or death. Primary outcome is time to formation of CR after initiation of ADT. Serum lipid levels (total cholesterol, high-density lipoprotein (HDL), low-density lipoprotein (LDL) and trigyserides) are analysed to test whether changes in serum cholesterol parameters during ADT predict length of treatment response. Furthermore, the trial will compare quality of life, cardiovascular morbidity, changes in blood glucose and circulating cell-free DNA, and urine lipidome during trial.

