### Inclusion and exclusion criteria

Inclusion criteria for participants are histopathologically confirmed metastatic adenocarcinoma of the prostate or high-risk M0 stage recurrent PCa for which androgen deprivation or antiandrogen therapy is initiated no longer than 3 months before recruitment, willingness to participate and signing of informed consent (figure 1).

Exclusion criteria for participants are regular statin use at the time of recruitment or within 6 months of it, previous adverse effects during statin therapy, familial hypercholesterolaemia or very high total cholesterol (9.3 mmol/L or above), clinically significant renal (serum creatinine above 170 µmol/L) or liver insufficiency (serum alanine aminotransferase more than two times above the upper limit of normal range), and use of drugs that may interact with statins (St John’s Wort, HIV protease inhibitors, ciclosporin, macrolide antibiotics, fucidic acid, phenytoin, carbamazepine, dronedarone or oral antifungal medication) (figure 1).

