### Study endpoints

Primary endpoint is the time to disease progression after starting ADT/antiandrogen therapy. Secondary endpoints are (1) PCa-specific mortality and overall survival, (2) change in serum cholesterol during the intervention and its role in predicting time to disease recurrence in the placebo arm, (3) occurrence of adverse tumour traits predicting development of castration resistance in circulating cell free DNA, (4) changes in fasting blood glucose during ADT, (5) occurrence of cardiovascular events during ADT and (6) Quality of life (QoL) during ADT.

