### Stored blood samples

Separate whole blood (for RNA and DNA isolation), plasma and serum samples are taken at each control visit at 6-month intervals and stored for mass-spectrometric and nuclear MR-based determination of serum lipidome. These samples will also be used for RNA and whole genome sequencing of mutations and genetic modifications predicting disease recurrence and metastasis, such as BRCA1/2, ERG, MYC, TP53, ATM, PTEN and AR splice variants.^34 35^ Also hypoxia markers will be measured.^36^

For participants with confirmed metastases in the bone or soft tissues, amount of cell free DNA from the plasma will be measured before ADT initiation and again at castration resistance development for sequencing and detection of genetic modifications predicting metastases.^34 35^ Selected patients are also imaged with positron emission tomography (PET) scan using 18F-2-nitroimidazolpentafluoropropylacetamide (EF5)^37^ to monitor hypoxia and fluorine-18-fluorodeoxyglucose positron emission tomography (FDG-PET) to evaluate immune responses^38^ in the primary tumour and the metastases during the atorvastatin intervention.

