**Figure 2 F2:**
[figure not shown]
Sample size estimation with power 0.8 as a function of HR. Calculation was made based on study by Harshman *et al.*^23^

The median time to disease progression is assumed to be 12–15 months for patients with de novo metastatic disease and 33 months for patients recurring after primary therapy.^3–7^ Therefore, the intervention will continue until castration resistance, death, or for maximum of 10 years. Post hoc follow-up will continue after the intervention. A 3 months’ difference in time to castration resistance between the study arms will be considered clinically significant.

It has to be noted that the number of studies published on this topic is low and, in the absence of randomised evidence on this topic, the power calculation is based on results of epidemiological study prone to residual bias. Therefore, an interim analysis will be performed after the first 100 participants have met the primary endpoint, that is, progressed into castration resistance. Without lifting the blinding, the power calculations are repeated to verify whether the chosen sample size has adequate statistical power to detect statistically significant difference of the effect size observed between the randomisation groups at that time. If the calculations suggest that a larger sample size is needed for the trial, the study protocol will be amended with updated recruitment target.

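### The primary endpoint is timed from ADT start although men may be recruited up to 3 months later; with no delayed entry, the absolute curves and medians can only be distorted upward, while the comparison between arms is not materially affected

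*Protocol article*

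**What the plan says.** The time origin is given three times, always as the start of hormonal treatment. The abstract (Methods and analysis) says "Primary outcome is time to formation of CR after initiation of ADT". Study endpoints says "Primary endpoint is the time to disease progression after starting ADT/antiandrogen therapy". Statistical methods says "Recurrence-free survival, that is, time from ADT initiation to castration resistance", which "will be analysed by using Kaplan-Meier (KM) estimator, stratified by study arm"; then "The statistical significance of the difference between the survival estimates is tested with log-rank test". Statistical methods adds that the Kaplan-Meier estimate will not be adjusted. Delayed entry is not mentioned.

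Inclusion and exclusion criteria admits men for whom "androgen deprivation or antiandrogen therapy is initiated no longer than 3 months before recruitment"; table 1 gives the same 3-month limit. Under Study flow, a man receives his study number and first study drug only after eligibility and consent are settled. The clock can therefore start up to 3 months before randomisation.

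**The concern.** A man randomised two months after ADT start is counted as at risk for those two months. During them he had neither atorvastatin nor placebo. He also could not have contributed an event, because a man who became castration resistant in that interval would not be entered in a trial of delaying castration resistance. An ordinary Kaplan-Meier estimate from ADT start places him in the risk set from day 0 all the same.

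At stake are the absolute results: the event-free curve in each arm, the early event-free proportions and the medians. Read as time under the intervention, they are too long by the gap. Read as time from ADT start, they are too long to the extent that some men progress before they could be enrolled.

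**Working it through.** The plan gives no figure for the gap or its effect, so there is nothing of its own to reproduce.

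**Inputs from the article.** Gap at most 3 months (Inclusion and exclusion criteria). Median time to progression 12 to 15 months for de novo metastatic disease and 33 months for recurrent disease; HR 0.65; 10% drop-out, so 360 of 400 men; minimum follow-up 12 months (Sample size calculation; Study flow).

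**Assumptions not in the article.** Gap uniform on 0 to 3 months, or 3 months for every man as the extreme; Weibull times with shape k; men who progress before entry are not enrolled; recruitment and randomisation coincide; 48-month accrual in the trial simulation.

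**1. Against time from randomisation.** Time from ADT start = gap + time from randomisation. The excess is each man's gap, with mean (0 + 3)/2 = 1.5 months if uniform. Simulated medians on the two clocks differ accordingly at every shape. For a true median of 12 months:
- k = 1: 13.47 − 11.99 = 1.48
- k = 1.5: 12.39 − 10.91 = 1.48
- k = 2: 12.13 − 10.64 = 1.49

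**2. Against true time from ADT start.** Let S(t) = 2^(−(t/m)^k) be the true curve with median m, and let π be the probability of still being event-free at entry. Beyond 3 months the estimate without delayed entry tends to S(t)/π. Setting S(t)/π = 1/2 gives an apparent median of

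m × (1 − log2 π)^(1/k), where π = (1/3)∫S(u)du over 0 to 3 for a uniform gap, and π = S(3) if every man enters at 3 months.

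Example, m = 12, k = 1, uniform gap: π = (1 − 2^(−3/12)) / ((3/12) ln 2) = 0.1591/0.1733 = 0.918. Then −log2 0.918 = 0.123, and 12 × 1.123 = 13.48, an excess of 1.48 months.

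| True median (months) | Shape k | π, uniform gap | Excess, uniform gap | Excess, all enter at 3 months |
|---|---|---|---|---|
| 12 | 1 | 0.918 | 1.48 | 3.00 |
| 12 | 1.5 | 0.966 | 0.39 | 0.98 |
| 12 | 2 | 0.986 | 0.12 | 0.37 |
| 15 | 1 | 0.934 | 1.48 | 3.00 |
| 15 | 1.5 | 0.976 | 0.35 | 0.88 |
| 15 | 2 | 0.991 | 0.10 | 0.30 |
| 33 | 1 | 0.969 | 1.49 | 3.00 |
| 33 | 1.5 | 0.992 | 0.24 | 0.60 |
| 33 | 2 | 0.998 | 0.05 | 0.14 |

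Simulation agrees within its error. For a uniform gap it gives an excess of about 1.5 months at k = 1, 0.2 to 0.4 at k = 1.5 and 0.03 to 0.13 at k = 2.

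**3. Comparison between arms.** The gap is fixed before allocation, so with no treatment effect the gap and the time from randomisation have the same joint distribution in both arms, and the log-rank test is valid on either clock. Results of 4,000 simulated trials per row (360 men, exponential times, uniform gap):

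| Control median | HR | Rejection rate, randomisation clock | ADT clock, no delayed entry | ADT clock, delayed entry | Difference in medians, randomisation / ADT clock |
|---|---|---|---|---|---|
| 12 | 1.00 | 0.052 | 0.053 | 0.053 | −0.04 / −0.04 |
| 12 | 0.65 | 0.940 | 0.941 | 0.941 | 6.47 / 6.47 |
| 15 | 0.65 | 0.932 | 0.932 | 0.931 | 8.15 / 8.16 |
| 33 | 0.65 | 0.777 | 0.777 | 0.778 | 17.86 / 17.85 |

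Chance imbalance in the gap is also small. A uniform 0 to 3 month gap has SD 3/√12 = 0.87, so with 200 men per arm the standard error of the difference in mean gap is 0.87 × √(2/200) = 0.087 months, under 3 days.

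**The case against.** The strongest reply is that the declared quantity is time from ADT start, so a difference of 1.5 months from the randomisation clock is merely the assumed mean gap and not an error in that quantity. This stands. Against the declared quantity, the excess reaches 1.5 months under uniform gaps only with a constant hazard from day 0. The article's definition of castration resistance makes that unlikely: it needs a PSA nadir, repeated rises and PSA above 2 ng/mL, or radiological progression, all at castrate testosterone. Few men would meet it within 3 months.

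Three stronger readings are tempting but unsupported.

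- That every man carries such time. Three months is a ceiling, and under Stored blood samples, for men with confirmed metastases, the "amount of cell free DNA from the plasma will be measured before ADT initiation and again at castration resistance development". Some men therefore appear to enter with little or no gap.
- That the excess should be weighed against the plan's threshold, "A 3 months’ difference in time to castration resistance between the study arms will be considered clinically significant". That threshold is a difference between arms, and a shift common to both arms cancels.
- That the results could not be set beside the 12 to 15 and 33 month figures. The Introduction gives those for men starting ADT, which fits an ADT clock at least as well, and the cited studies' time origins are not stated.

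It can also be said that the promised statistical analysis plan could add delayed entry. It could, but the article already fixes a time origin before randomisation and an ordinary Kaplan-Meier estimate, so the choice has to be changed and not only filled in.

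**Conclusion.** The point holds for the absolute estimates only. The clock starts before randomisation for men with a gap, no delayed entry is described, and any resulting distortion of the curves and medians is upward. Read as time from randomisation, the excess is the gap itself: 0 to 3 months, with mean 1.5 if uniform. Read as true time from ADT start, under a uniform gap, it runs from about 1.5 months with a constant hazard down to between a few hundredths of a month and about 0.4 months at Weibull shape 1.5 to 2. The lower part of that range is the more plausible given the event definition. If every man entered at the limit, the constant-hazard figure would be 3 months. The gap distribution and the hazard shape are assumptions; the article gives neither.

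A reader might infer that the treatment effect is biased. The documents do not support that: the gap precedes randomisation and is balanced in expectation, and type I error, power and the difference in medians were the same on both clocks to within simulation error. This is an improvement available at no cost, not a flaw in the trial's main inference.

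**What to change.** In the abstract, Study endpoints and Statistical methods, define the primary endpoint as time from randomisation to castration resistance, and apply the Kaplan-Meier estimate and log-rank test on that clock. If time since ADT start is wanted, present it as a supporting analysis in which each man enters the risk set at randomisation (left truncation), noting that the risk set in the first 3 months may be small. Report the distribution of the ADT-to-randomisation gap by arm.

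The cost is a wording change, best made in the promised statistical analysis plan and before unblinding. It needs only the allocation date and the ADT start date, and the current definition already requires the latter. The simulations show no loss of power (0.940 against 0.941 at a 12-month control median and HR 0.65), so the sample size need not change on this account.

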Study type	Interventional, allocation: randomised, Intervention model: parallel assignment with 1:1 allocation ratio, Masking: double blind (subject, caregiver, investigator, outcomes assessor), Primary purpose: prevention, phase III
Date of first enrolment	July 2019
Target sample size	400
Recruitment status	Recruiting
Primary outcome(s)	Castration resistance
Key secondary outcomes	Lipid levels, Prostate cancer mortality and overall survival, Circulating cell free DNA, Fasting blood glucose, Occurrence of cardiovascular events during ADT, Quality of life

ADT, androgen deprivation therapy.

The study will be carried out in collaboration between urological departments of University Hospitals and central hospitals in Finland, the Herlev University Hospital in Denmark, the Tartu University Hospital in Estonia and Vestfold Hospital Trust in Norway (table 1).

Study data are collected and managed using REDCap electronic data capture tools hosted at Tampere University.^31 32^ Only the primary investigators, study nurses and registered study coinvestigator from each participating site will have access to the platform. All laboratory results, symptoms and results from imaging studies done at the discretion of the attending clinicians are recorded in the database. All clinical decisions besides the study drug, for example, use of early chemotherapy, abiraterone or other drugs in adjunct with ADT will be up to the discretion of the attending clinician and allowed but will also be recorded in the REDCap database.

Follow-up is continued until development of castration resistance, death or maximum of 10 years. Participants are given the opportunity to carry on with the intervention even after development of castration resistance to observe effects on survival. Unblinding will be performed after recruitment target has been reached and all participants have been followed for minimum of 12 months.

Castration resistance is defined as either PSA progression (three consecutive rises of PSA measured at least 1 week apart with two >50% increases over the nadir and PSA >2 ng/mL) or radiological progression (appearance of two or more lesions in bone scan or soft tissue enlargement as per RECIST criteria) while serum testosterone is at the castrate level (<50 ng/mL or 1.7 nmol/L).

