Control visits are scheduled at 6-month intervals to suit common clinical practice. Control visits are done by a clinician, complemented with measurements done by a research nurse. For each control visit the participant returns remaining capsules from the previously delivered ration and will receive a new one according to his study number. Number of the remaining capsules will be counted and saved in the REDCap, trial database, to monitor compliance. In every visit, serum PSA (ng/mL), lipid levels (total cholesterol, high-density lipoprotein (HDL), low-density lipoprotein (LDL) and triglycerides, mmol/L), alkaline phosphatase (U/L), creatinine (μmol/L), and fasting glucose (mmol/L) will be measured (table 2) and the participant is asked about symptoms that are suggestive of metastases and about possible adverse effects of the study drug. Serum creatine kinase (U/L) and alanine aminotransferase (U/L) is also measured at each visit.

Blood samples are taken and stored at 6-month intervals to monitor changes in tumour markers and occurrence of adverse tumour characteristics after initiation of ADT. QoL during the intervention will be charted once a year using validated WHOQOL-BREF QoL questionnaire.^33^

Follow-up is continued until development of castration resistance, drop out from the study, death or maximum of 10 years. Participants developing castration resistance are given an opportunity to carry on with their assigned treatment as statins have been linked to longer cancer-specific survival. Unblinding will be performed after recruitment target has been reached and all participants have been followed for minimum of 12 months.

PCa treatment apart from the study drug will be up to the discretion of the attending clinician. All laboratory results, symptoms and possible imaging results will be recorded in the REDCap database. All clinical decisions regarding early chemotherapy and imaging will be made on the discretion of the clinician and recorded in the REDCap database.

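### The primary variable is named recurrence-free survival but counts only castration resistance, so Kaplan-Meier censors deaths and modestly overstates the proportion who become resistant

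*Protocol article*

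**What the plan says.** The Statistical methods section gives the primary analysis variable a name and a definition in one sentence: "Recurrence-free survival, that is, time from ADT initiation to castration resistance, will be analysed by using Kaplan-Meier (KM) estimator". The arms are compared by an unadjusted log-rank test.

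The rest of the article agrees with the definition, not with the name:

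- Abstract: "Primary outcome is time to formation of CR after initiation of ADT".
- Study endpoints: "Primary endpoint is the time to disease progression after starting ADT/antiandrogen therapy".
- Sample size calculation, on the interim analysis: the trigger is that the "first 100 participants have met the primary endpoint, that is, progressed into castration resistance".
- Study setting: "Castration resistance is defined as either PSA progression" or radiological progression, in either case with testosterone at castrate level. Death is not a component.

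On the end of observation, Study setting says: "Follow-up is continued until development of castration resistance, death or maximum of 10 years". Study flow adds withdrawal to that list: "Follow-up is continued until development of castration resistance, drop out from the study, death or maximum of 10 years". Prostate-cancer mortality and overall survival are secondary endpoints, and risk of death is analysed separately by Cox regression.

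**The concern.** In a recurrence-free survival endpoint, death is an event. Here it is not. With CR as the only event and observation stopping at death, a man who dies first becomes an ordinary censored observation. Three things follow.

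1. **The label misleads.** A reader of the results would take a recurrence-free survival curve to show the proportion alive and free of CR. The planned curve does not show that.
2. **The curve overstates CR.** Kaplan-Meier with deaths censored estimates how many men would reach CR if nobody died first. The proportion who actually reach CR is lower.
3. **Some censoring is probably informative.** CR needs a series of PSA rises or an imaging finding. PSA is scheduled every six months, so three rises found at scheduled visits alone put 12 months between the first and the third. Imaging is not scheduled: "results from imaging studies done at the discretion of the attending clinicians are recorded in the database". A man who deteriorates quickly can die of prostate cancer before the definition is met. Kaplan-Meier then assumes that his later risk of CR would have matched that of the survivors, which is hard to believe for such a death.

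The ethics section credits atorvastatin with cardiovascular benefit, and cardiovascular events are a secondary endpoint. The number of men removed by death could therefore differ between arms.

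**Working it through.** **Step 1: is death an event anywhere?** No. The five places listed above count CR or progression only. No section names death as a primary event or as a competing event, and none states a censoring rule. Censoring at death is therefore an inference from three stated facts: the event is CR, observation stops at death, and the estimator is Kaplan-Meier.

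**Step 2: inputs for the size.** The plan gives no figure for deaths before CR, so there is none to reproduce.

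- Median time to CR, metastatic disease: 12-15 months (Sample size calculation). The midpoint, 13.5 months, is used.
- Median, recurrent disease: 33 months. The Introduction calls this failure-free survival; the Sample size calculation uses it as time to progression, and so does this check.
- Yearly rate of death without CR: d = 0.02 to 0.05. **This is an assumption.**
- Mix of disease types: 200 metastatic and 200 recurrent. **This is also an assumption.**
- Constant hazards.

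**Step 3: formulas.** The CR hazard is h = ln 2 / median in years.

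- Metastatic: 0.693/1.125 = 0.616 per year.
- Recurrent: 0.693/2.75 = 0.252 per year.

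At 3 years:

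- One minus Kaplan-Meier = 1 − exp(−3h)
- True cumulative incidence of CR = h/(h+d) × [1 − exp(−3(h+d))]
- Proportion dying before CR = d/(h+d) × [1 − exp(−3(h+d))]

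**Step 4: results at 3 years.**

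| Group | d | 1 − KM | True incidence of CR | Excess (points) | Died before CR |
|---|---|---|---|---|---|
| Metastatic | 0.02 | 84.3% | 82.5% | 1.8 | 2.7% |
| Metastatic | 0.05 | 84.3% | 80.0% | 4.3 | 6.5% |
| Recurrent | 0.02 | 53.1% | 51.7% | 1.4 | 4.1% |
| Recurrent | 0.05 | 53.1% | 49.7% | 3.3 | 9.9% |

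Worked example, metastatic with d = 0.05: h+d = 0.666; 1 − exp(−1.998) = 0.864; 0.616/0.666 × 0.864 = 0.800.

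Men dying before CR by 3 years:

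- d = 0.02: 200 × (0.0268 + 0.0410) = 13.6, about 14.
- d = 0.05: 200 × (0.0649 + 0.0986) = 32.7, about 33.

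**Step 5: can a supportive analysis counting deaths be informative?** By Schoenfeld's formula (80% power, two-sided 5%; the article does not state sidedness), HR 0.65 needs 170 events. Suppose deaths make up 10% of control-arm first events and are unaffected by treatment. The composite HR is then 0.9 × 0.65 + 0.1 × 1 = 0.685, which needs 220 events. At the plan's CR proportions of 58% and 75% (mean 66.5%), 400 men give 266 CR events, and 360 men after 10% drop-out give 239, before any deaths are added.

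**The case against.** The strongest reply is that this is a naming slip. The sentence defines its own label and every other section agrees, so nobody would code a death as a primary event. That stands: the definition is consistent, and only the name is wrong.

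Second, log-rank on time to CR with deaths censored is a legitimate cause-specific comparison. That also stands. It tests whether the CR hazard differs among men still alive and free of CR, and different death rates between arms do not by themselves invalidate it. A reader might infer from the cardiovascular argument that the primary test is biased. The documents do not support that: it would require dependence between death and later CR risk, and they give nothing from which to estimate such dependence.

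Third, a reader might infer that men who die of prostate cancer are scored as never having progressed. They are not. They count as event-free up to death and then leave the risk set. Their deaths are also captured in the secondary mortality endpoints.

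Fourth, the numbers may be small. The Introduction puts median CR well before median death (12-15 against 45 months; 33 against 70 months). The counts above are deaths from any cause, and no figure for prostate-cancer deaths without documented CR can be derived. Letting the same hazards run without limit gives 21-48 men, from 200 × (3.1% + 7.4%) to 200 × (7.5% + 16.6%). The trial can be unblinded once the last man has 12 months of follow-up, so that larger range should not be quoted as the expected count.

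Finally, a detailed statistical analysis plan is promised and may settle the handling of deaths. The absence of a censoring rule is therefore not held against the article. The name and the estimator, however, are stated here.

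**Conclusion.** The point holds as a low-cost improvement. The name contradicts the definition, and the stated estimator overstates the proportion reaching CR by about 1-4 percentage points at 3 years. That size rests on an assumed 2-5% yearly rate of death without CR, constant hazards and the plan's own medians. The corresponding 14-33 of 400 men also assumes an equal mix of disease types. Prostate-cancer deaths without documented CR are handled as non-informative censoring, which is doubtful, but their number is unknown.

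The log-rank comparison and the sample size are not undermined. Nor does the article support insisting that prostate-cancer death become a primary event. That choice would make the primary endpoint depend on cause-of-death attribution and would depart from the CR proportions behind the sample size. It is optional.

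**What to change.** 1. In Study endpoints and Statistical methods, name the primary endpoint *time to castration resistance*. Keep the log-rank test and state that it compares cause-specific hazards, with deaths before CR censored.
2. Show CR by arm as Aalen-Johansen cumulative incidence, with death before CR as a competing event, in place of one minus Kaplan-Meier.
3. Add a pre-specified supportive analysis of CR or death from any cause, and use the name recurrence-free survival only for that.
4. Fix all of this before unblinding, so that the handling of deaths cannot be chosen after the results are seen.

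The cost is some wording, a little extra analysis and slightly lower reported CR proportions. No new data are needed, because deaths are already collected for the mortality endpoints.
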